## Abstract

**Background:** Despite on-going efforts to better understand dysregulated eating, the olfactory-gustatory deficits and food preferences in eating disorders (ED), and the mechanisms underlying the perception of and responses to food properties in anorexia nervosa (AN) and bulimia nervosa (BN) remain largely unknown; both during the course of the illness and compared to healthy populations. It is, therefore, necessary to systematically investigate the gustatory perception and hedonics of taste in patients with AN and BN. To this end, we will examine whether aversions to the taste of high-calorie food is related to the suppression of energy intake in restricting-type AN, and whether an increased hedonic valence of sweet, caloric-dense foods may be part of the mechanisms triggering binge-eating episodes in BN. In addition, the role of cognitions influencing these mechanisms will be examined.

**Method:** In study 1, four mixtures of sweet-fat stimuli will be presented in a sensory two-alternative forced-choice test involving signal detection analysis. In study 2, a full-scale taste reactivity test will be carried out, including psychophysiological and behavioral measures to assess subtle and covert hedonic changes. We will compare the responses of currently-ill AN and BN patients to those who have recovered from AN and BN, and also to those of healthy normal-weight and underweight individuals without any eating disorder pathology.

**Discussion:** If taste response profiles are differentially linked to ED types, then future studies should investigate whether taste responsiveness represents a useful diagnostic measure in the prevention, assessment and treatment of EDs. The expected results on cognitive mechanisms in the top-down processes of food hedonics will complement current models and contribute to the refinement of interventions to change cognitive aspects of taste aversions, to establish functional food preferences and to better manage food cravings associated with binge-eating episodes. No trial registration was required for this protocol, which was approved by the Swiss ethics committee (CER-VD, n° 2016-02150) and the Ethics Review Panel of the University of Luxembourg.

## Background

Anorexia nervosa (AN) and bulimia nervosa (BN) are serious, often treatment-refractory mental illnesses, including medical complications, frequent comorbidity, and high mortality (Westmoreland et al., 2016). Despite extensive research in eating disorders (EDs), the core phenomenon of extremes in appetite (too little or too much) and the perception of food taste remains scarcely investigated. This is surprising as the perception of food plays an important role in the maintenance of disordered eating behaviors (e.g., restrictive food intake, binge-eating of palatable food) and ED interventions (e.g., targeting forbidden foods, unbalanced diet). This research aims to shed light on the gustatory and taste hedonic responses to high-calorie food in AN (restrictive-type) compared to BN and healthy individuals, and how they are biased by cognitions of gaining weight. The novel and most critical assumption of our approach is that the effect of food on eating behavior arises actively through perceptual processes (i.e., within the brain), not just passively from physicochemical properties of the foods themselves (Berridge et al., 2010).

Previous research on gustometry have found decreased or altered taste sensitivity and hypogeusia in AN and BN patients (Casper et al., 1980; Drewnowski et al., 1987b; Nakai et al., 1987; Aschenbrenner et al., 2008), which are often assumed to facilitate self-starvation via decreased taste qualities of feeding in EDs. Factors known to affect taste perception in individuals with EDs include the reduced number of fungiform papillae on the tongue in AN and damages in the palate caused by vomiting in BN (Rodin et al., 1990; Wöckel et al., 2007). These findings, however, remain controversial as other studies have not found such abnormalities (Di Costanzo et al., 1998; Vocks et al., 2011; Goldzak-Kunik et al., 2012; Dazzi et al., 2013), and deficits seem to be rather a consequence than a cause of low body weight, metabolic abnormalities, duration of the illness or malnutrition. Gustatory alterations are partially reversible after weight restoration (Aschenbrenner et al., 2008), and amenable to psychological interventions (Goldzak-Kunik et al., 2012). For example, Nozoe et al. (1996) found taste responsiveness in AN to improve after behavior therapy, even prior to any increase in body weight. AN patients have also been shown to respond differently to swallowed than expectorated sugar solutions, suggesting that responses are driven by the expectancy of calories rather than the taste *per-se* (Eiber et al., 2002). Thus, cognitions concerning the fear of weight gain are likely to affect the experience of taste perception, closing a pathological circle, which maintains the core symptoms of AN (Monje Moreno et al., 2014).

Overall, gustatory experiences are reported by BN patients as less intense compared with healthy controls, though the average scores are within the range of normogeusia (Nakai et al., 1987; Jirik-Babb and Katz, 1988). When flavors are applied to the tongue instead of sipped (e.g., using the taste strip methodology), lowered gustatory sensitivities have been found (Rodin et al., 1990; Aschenbrenner et al., 2008; Dazzi et al., 2013) in BN patients. As whole-mouth taste experience is not altered and only a few studies with mixed results have examined the gustatory response in BN, it remains unclear whether these alterations are a consequence or a predisposing factor for BN.

Importantly, taste sensations elicit strong affective^1^ responses (Vögele et al., 2018). While altered hedonic reactions to pleasant-tasting food are a feature of AN, it is unclear whether this is due to increased disliking of high-caloric products, or reduced liking associated with low sensitivity to food pleasantness. The current evidence does not point to a deficit in experiencing taste hedonics in AN, as self-report measures show similar responses to low-energy foods, aversive tastes or sucrose solutions in the sip-and-spit paradigm compared to controls (Eiber et al., 2002; Jiang et al., 2010; Szalay et al., 2010). Rather, individuals diagnosed with AN show enhanced dislike for the taste of high-energy foods (Drewnowski et al., 1987b; Sunday and Halmi, 1990; Stoner et al., 1996; Tóth et al., 2004), especially those with restrictive-type AN (Cowdrey et al., 2013). Perhaps even more important, hedonic ratings tend to be strongly reduced by an overriding fear of weight gain in paradigms where sucrose solutions are swallowed compared to when these solutions are spat out (Eiber et al., 2002). The use of self-report measures for the investigation of hedonics in individuals with AN, however, is limited as they are often characterized by difficulties in detecting and describing their own and others emotions (Bydlowski et al., 2005; Vögele et al., 2018). Therefore, objective measures (i.e., those less prone to be affected by conscious control) to assess hedonic reactions to taste (e.g., facial responses) are needed. To the best of our knowledge, only three studies have applied either facial electromyographic activity (Friederich et al., 2006; Soussignan et al., 2011) or orofacial expression analysis (Szalay et al., 2010) to assess taste hedonics in AN. Together, these studies suggest reduced automatic pleasantness processing and weaker reactivity in AN compared to non-eating disordered controls. Nevertheless, these results remain inconclusive, as other potential mediators of food hedonics (e.g., exercise, depressive mood, hunger, satiety states, and food reward sensitivity) were not considered.

In BN patients, results on taste hedonics are inconsistent and vary with respect to the dimensions of calorie content (high vs. low), taste (fat vs. sweet) and history of AN. While both AN and BN patients avoid fat taste, only bulimics without a history of AN show higher liking ratings for high-sweet taste stimuli compared to controls (Garner et al., 1978; Drewnowski et al., 1987a; Sunday and Halmi, 1990; Franko et al., 1994), but without differences for low-sweet taste solutions (Rodin et al., 1990). Interestingly, compared with restrictive AN and healthy controls, a greater proportion of BN women (and binge-eating/purging AN) reported use of artificially sweetened low-calorie products and “patients described consuming the sweetener directly from the packet, using 100 or more packets daily” (Klein et al., 2006, p. 344), suggesting an increased drive for sweet orosensory stimulation. Moreover, during binges, BN individuals tend to eat high-caloric foods they would otherwise avoid, and their primary choice of foods is high in carbohydrates (van der Ster Wallin et al., 1994). Whether binge eating is characterized by craving for those very sweet stimuli remains largely unexplored.

In summary, these findings suggest that taste disturbances in AN and BN are rather a consequence than the cause of the respective ED. It remains unclear, however, whether these disturbances are a result of the physical (e.g., body mass index [BMI], physiological dysfunction) or the psychological changes associated with AN/BN (e.g., biased cognitions, mood, depressive mood). Concerning taste hedonics, it is important to better understand the processes motivating approach/avoidance behavior with regards to low- and high-calorie foods (Cowdrey et al., 2013; Wolz et al., 2015). Based on the current literature, we would argue that the perception of calorie intake and the fear of weight gain are responsible for the avoidance of high-caloric food in AN and BN, mainly through two mechanisms: a first mechanism (more intentional) is based on resisting food craving actions in BN (who indeed like high-sweet food) and another (more visceral) is based on learned taste aversion in those individuals with restricting-type AN (Bernstein and Borson, 1986), who respond to palatable food as if its taste were disgusting (Chapman and Anderson, 2012). An explanation about how the mechanisms contribute to caloric restriction and binge eating is offered in Figure 1. The main aim of the present research, therefore, is to systematically investigate the gustatory perception and hedonics of taste. We will examine whether aversions to the taste of high-calorie food is related to the suppression of energy intake in restricting-type AN, and whether an increased hedonic valence of sweet, caloric-dense foods may be part of the mechanisms triggering binge-eating episodes in BN. We will also examine the role of cognitions influencing these mechanisms.

**Figure 1 F1:**
[figure not shown]
Serial hierarchical processing of taste (Wolz et al., 2015) at the sensory (blue), reward/hedonic (green), and cognitive level (red) via bottom-up influences. In restricting AN **(A)**, biased cognitions about body weight (e.g., “this food increases body weight”) make one feel bad while eating and these negative feelings extend to the affective value of taste (e.g., disgust; Bernstein and Borson, 1986) making caloric food taste worse (taste aversion) and ceasing intake. It is worth noting that cognitions can reach down into the taste system in the orbitofrontal cortex, which controls how pleasant a taste stimulus is (Grabenhorst et al., 2008; Rolls, 2015). In BN **(B)**, there is a motivational conflict between avoiding food because of anticipation of unpleasant feelings underlying becoming fat and the enhanced pleasant reactions to sweet taste, which finally override the inhibitory cognitive control to resist food craving and exacerbate food consumption, and thus binge-eating episodes. (–) aversive or (+) appetitive affective activation.

Hypothesis

H1: If perceptual disturbances in AN and BN are related to biased cognitions about gaining weight rather than to gustatory deficits or BMI, then AN and BN patients should respond with similar sensory performance but higher response bias scores in a discrimination test, (1) compared to non-ED underweight, normal-weight and illness-recovered controls, and (2) during a swallowing compared with a sip-and-spit condition.H2: If fear of weight-gain in restricting-type AN elicits taste aversion, then facial electromyographical, facial expression, and autonomic and subjective correlates of disgust (Kappas, 2003; Kreibig, 2010) while tasting high-sweet and high-fat foods should be observed compared to (1) stimuli of low-sweet and low-fat foods; (2) non-ED underweight, normal-weight, illness-recovered controls and (3) BN patients; and (4) especially during the swallowing compared with the sip-and-spit condition.H3: If avoidance of energy-rich foods in BN reflects a cognitive preoccupation about the increased liking of very sweet tastes associated with gaining weight, then facial electromyographical, facial expression, and autonomic and subjective correlates of pleasure (Kappas, 2003; Kreibig, 2010) while tasting high-sweet foods should be observed compared to (1) fat and low-sweet stimuli; (2) non-ED underweight, normal-weight, illness-recovered controls and (3) restrictive-type AN; and (4) no differences between swallowing and sip-and-spit conditions.

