### Food samples

In contrast to pure tastes commonly used in research on gustatory perception, four ordinary, more ecologically valid mixtures of chocolate ice cream containing low vs. high levels of fatness and low vs. high levels of sweetness (Table 5) will be presented in 100-ml disposable Styrofoam cups at room temperature and in counterbalanced order across participants. Chocolate ice cream was selected according to the assumptions that chocolate ice cream is likely to be a forbidden food for AN and BN participants, and that AN participants can be expected to have strong aversive associations. The samples are stored at minus 18°C. Optimal mixtures were elaborated at the School of Agricultural, Forest and Food Sciences (Department of Food Science & Management; Bern University of Applied Sciences) and obtained considering previous studies on taste sensory and hedonic ratings (Sunday and Halmi, 1990) and surface response method (Drewnowski et al., 1987b) in AN and BN. Assuming an all-or-nothing (i.e., dichotomous) approach to food in AN and BN, regardless of the fat or sucrose levels, the specific ingredients of the samples were further selected in order to increase differences across ice cream samples in terms of sweetness, creaminess, expectation of caloric content and hedonic reactions (Table 6). In this sense, although previous studies have found pronounced aversion to the sugar-fat mixtures in AN patients, variability in aversive scores across combinations of sweet taste and fat together has also been demonstrated. For instance, differences comparing liking response profiles as a function of increasing sucrose content (0–20% wt/wt) separately from different fat samples (0.1–52.7% fat wt/wt) have been observed in AN (restrictive) and bulimic patients, and in both currently-ill and recovered patients (e.g., Drewnowski et al., 1987b; Sunday and Halmi, 1990). Finally, while water will be used as control stimulus, two savory (high-fat and low-fat) sauces will be added in study 2 as additional comparators to demonstrate that any differences detected are unique to sweet-fat foods in BN patients as previous research suggests.

**Table 5 T5:** Characterization of the food samples with low and high content of fatness and sweetness.

**Components**	**Low fatness and low sweetness**	**Low fatness and high sweetness**	**High fatness and low sweetness**	**High fatness and high sweetness**
Dry matter (%)	30.0	30.0	39.5	39.5
Fat content (%)	1.2	1.2	11.4	11.4

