Carbohydrate (g)	21.8	21.8	22.1	22.1
Protein (g)	4.7	4.8	4.8	4.8
Fat (g)	1.2	1.2	11.9	11.9
Kcal total	117.0	117.3	215.1	215.4
Kcal (%)	54.3	54.4	99.9	Reference = 100
Relative sweetness	14.45	28.01	14.76	28.8

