### The expected results

Concerning the study 1, the main results to be expected are that a different and reduced C (*C* < 0) and (ß < 1) are expected in currently-ill AN and BN patients compared to non-ED underweight, normal-weight and illness-recovered controls, and during a swallowing compared with a sip-and-spit condition. Reduced C and ß-values would show a response bias to say, “Yes, the gaining weight-related attribute [sweetness, creaminess and caloric content] is present.” By contrast, patients will have a similar high d′ value compared with control groups, which means that all the participants have a good sensory discrimination.

Concerning the study 2, it is mainly predicted that restricting-type AN will show evidence of reduced verbal ratings as well as bodily higher corrugator activity, disgust facial expressions and heart rate acceleration in response to high-sweet and high-fat foods compared to stimuli of low-sweet and low-fat foods; non-ED underweight, normal-weight, illness-recovered controls and BN patients; and especially during the swallowing compared with the sip-and-spit condition. On the other hand, higher zygomatic muscle activity and more smiles expressions in response to very sweet tastes will be expected to observe in BN compared to fat and low-sweet stimuli; non-ED underweight, normal-weight, illness-recovered controls and restrictive-type AN; and no differences between swallowing and sip-and-spit conditions.

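### H3(1) does not say which ice creams are target and comparator, and any comparator defined by fat lets the fat effect into a test meant for sweetness

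*Protocol article*

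**What the plan says.** - **Hypothesis, H3(1).** Correlates of pleasure in BN "while tasting high-sweet foods should be observed compared to (1) fat and low-sweet stimuli". The expected-results section repeats the pairing: more zygomatic activity and smiling "in response to very sweet tastes will be expected to observe in BN compared to fat and low-sweet stimuli".
- **Background, main aim.** The BN question is "whether an increased hedonic valence of sweet, caloric-dense foods may be part of the mechanisms triggering binge-eating episodes in BN".
- **Background, earlier findings.** "While both AN and BN patients avoid fat taste, only bulimics without a history of AN show higher liking ratings for high-sweet taste stimuli" compared with controls.
- **Food samples, Table 5.** The four ice creams are low-fat/low-sweet, low-fat/high-sweet, high-fat/low-sweet and high-fat/high-sweet. Their energy, in that order, is "Kcal total 117.0 117.3 215.1 215.4". The ingredient list of the two samples at each fat level differs only in aspartame.
- **Planned analysis, Study 2.** A mixed three-way ANOVA with group (six levels), testing condition (two) and food sample (four levels). I take the four levels to be the ice creams; the section does not split them into sweetness and fat.

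**The concern.** H3 is directional and concerns sweetness, but its comparator is described partly by fat. In a crossed set, *high-sweet* and *fat* are not alternatives, because one sample is both. The reader must choose how to parse the comparator, and the choices estimate different quantities. An omnibus test of a four-level factor does not settle it, since that test has no direction and no target sample.

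At stake is what a positive result would mean. H3 is the article's test of increased liking of very sweet taste in BN. If the fat effect enters the contrast, dislike of fat could pass for liking of sweetness. The aim adds a second question, about food that is both sweet and high in energy, which the H3 wording does not separate from sweetness alone.

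**Working it through.** **1. Inputs.** The documents give the 2 x 2 structure and the energy values. They give no response effects, so s (sweetness effect at low fat), f (fat effect at low sweetness) and i (interaction) are symbols, and the values in step 3 are assumptions.

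Cell means relative to low-fat/low-sweet (LFLS): LFLS = 0; low-fat/high-sweet (LFHS) = s; high-fat/low-sweet (HFLS) = f; high-fat/high-sweet (HFHS) = s + f + i.

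**2. Contrast under each reading of H3(1).**

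- A. Sweetness averaged over fat: (LFHS + HFHS)/2 - (LFLS + HFLS)/2 = **s + i/2**. No f.
- B. Comparator is the single HFLS sample: (LFHS + HFHS)/2 - HFLS = (2s + f + i)/2 - f = **s - f/2 + i/2**.
- C. *Fat* stands alone and HFHS is on both sides: (LFHS + HFHS)/2 - (HFLS + HFHS)/2 = (LFHS - HFLS)/2 = **(s - f)/2**. HFHS cancels and contributes nothing.
- D. *Fat* stands alone and HFHS is comparator only: LFHS - (HFLS + HFHS)/2 = **s/2 - f - i/2**.

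**3. Assumed patterns.**

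| s, f, i | A | B | C | D |
|---|---|---|---|---|
| 1, 0, 0 (sweetness only) | 1.00 | 1.00 | 0.50 | 0.50 |
| 0, -1, 0 (fat avoidance only) | 0.00 | 0.50 | 0.50 | 1.00 |
| 1, -1, 0 (both, as in the Background) | 1.00 | 1.50 | 1.00 | 1.50 |
| 1, 1, 0 (fat liked) | 1.00 | 0.50 | 0.00 | -0.50 |

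The second row matters most: with no liking of sweetness at all, B, C and D are positive and only A is zero.

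**4. Group comparisons.** For H3(2) and (3), take differences between groups. Under B, BN minus a control group gives (difference in s) - (difference in f)/2 + (difference in i)/2. If BN patients avoid fat more than controls, half of that gap counts towards H3.

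**5. Precision.** With equal, independent residuals, the variance is proportional to the sum of squared weights. A: 4 x 0.25 = 1. B: 0.25 + 0.25 + 1 = 1.5. B's standard error is sqrt(1.5) = 1.22 times that of A.

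**6. The aim.** At each fat level, raising sweetness adds 0.3 kcal (117.3 - 117.0 and 215.4 - 215.1). LFHS has 117.3/215.4 = 54% of the energy of HFHS, so by energy only HFHS is both high-sweet and calorie-dense. Whether sweetness is liked more at high energy is the interaction, (HFHS - HFLS) - (LFHS - LFLS) = i. Sweetness alone is A. These are two questions.

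**The case against.** **The comparator may be one sample.** Tables 5 and 6 name samples by both attributes, so H3's phrase can be read as the high-fat/low-sweet sample, and no section names the high-fat/high-sweet sample as a comparator. This stands: the double role depends on how the phrase is parsed. But that reading is B, which carries half the fat effect and leaves out low-fat/low-sweet.

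**The BN prediction is about sweetness.** Figure 1 and the Study 2 procedure also place it there. That is true, and it supports contrast A as the intended test. The comparator wording does not match that intention.

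**Contrasts belong in the analysis plan.** Detailed weights can be left there. The point here is the hypothesis as printed, not the absence of weights.

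**Perceived calories.** In Table 6 (N = 5, normal weight) rated caloric content is 5.83 for low-fat/high-sweet and 5.21 for high-fat/low-sweet. *Caloric-dense* could therefore mean perceived energy. The statement that only one sample qualifies holds for actual energy.

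A reader might infer more, without support:

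- *That the food section makes the high-fat/high-sweet sample the BN target.* The savory sauces are added "to demonstrate that any differences detected are unique to sweet-fat foods in BN patients", which sets ice cream against sauce. The Abstract applies the same label to all four samples: "four mixtures of sweet-fat stimuli will be presented".
- *That H2(1) overlaps in the same way.* Its wording naturally means the two extreme samples.
- *That the sign of H3 flips between passages.* D turns negative only when f + i/2 > s/2, and the documents give no such values. With a pure sweetness effect all four readings agree in sign. With liked sweetness, avoided fat and no interaction, all four stay positive.

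**Conclusion.** The point holds as an unclear and confounded comparison in H3(1), repeated in the expected results and not resolved by a four-level food factor. On one reading the high-fat/high-sweet sample is both target and comparator. On the other, half of any fat effect enters the result, so fat avoidance alone could look like support for H3. The aim's sweet, calorie-dense food is a separate question that the hypothesis does not isolate.

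The size rests on assumed effects: one unit of fat avoidance produces +0.5 under the single-sample reading and 0 under the sweetness contrast. The direction of the risk does not rest on assumption alone, because the Background itself reports fat avoidance in BN. This is a defect of interpretation that should be corrected; it does not undermine the design, since the crossed samples already allow the clean test.

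**What to change.** In the Hypothesis, Planned analysis and expected-results sections:

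1. Replace the four-level food factor for the ice creams with sweetness (2) x fat (2). The same 3 degrees of freedom split into 1 + 1 + 1, so nothing is lost.
2. Test H3(1) with [(low-fat/high-sweet minus low-fat/low-sweet) + (high-fat/high-sweet minus high-fat/low-sweet)]/2, within currently-ill BN and as a difference between groups.
3. State the sweetness x fat interaction as the separate test of the sweet, calorie-dense aim. As a difference of differences its squared weights sum to 4 against 1 for the sweetness contrast, so its standard error is twice as large; say that it will be less precise.
4. If a comparison with fat stimuli is kept, state it separately and name its samples.

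The cost is wording and model specification. No new samples, visits or data are needed.
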